**Primary outcomes (Aerobic capacity)**		
Peak oxygen uptake (VO_2_peak)	Peak oxygen uptake in the last 30 s during IET	mL/min, mL/min/kg
Peak work rate (Ppeak)	Maximal work rate during IET	W
Peak heart rate (HRpeak)	Maximal heart rate during IET	beats/min
Peak ventilation rate (V_E_peak)	Peak ventilation rate in the last 30 s during IET	L/min
Peak respiratory rate (R_f_peak)	Peak respiratory rate in the last 30 s during IET	1/min
Peak respiratory exchange ratio (RERpeak)	Value of the oxygen uptake and carbon dioxide output relationship at peak oxygen uptake	dimensionless
Gas exchange threshold (GET)	Oxygen uptake at the point at which carbon dioxide output begins to increase more rapidly in proportion to oxygen uptake during IET. Estimated using the v-slope method and standard gas exchange criteria	mL/min, mL/min/kg
Oxygen cost of work (ΔVO_2_/ΔP)	Δ oxygen uptake/Δ work rate	mL/min/W
Heart rate response (ΔHR/ΔVO_2_)	Δ heat rate/Δ oxygen uptake	beats/mL/min
Peak oxygen pulse (VO_2_peak/HRpeak)	Peak oxygen uptake/peak heart rate	mL/beat
Time constants of oxygen uptake during on-/off-transition (τ)	Time taken for oxygen uptake to reach 63% of its increment magnitude, when the response is modelled as a mono-exponential function during CLT	s
Steady-state increase in oxygen uptake (ΔVO_2_)	Steady-state increase in oxygen uptake following a step increase/decrease in exercise intensity during CLT	mL/min, mL/min/kg
Steady-state increase in heart rate (ΔHR)	Steady-state increase in heart rate following a step increase/decrease in exercise intensity during CLT	beats/min
Steady-state increase in ventilation rate (ΔV_E_)	Steady-state increase in minute rate following a step increase/decrease in exercise intensity during CLT	L/min
Steady-state increase in respiratory rate (ΔR_f_)	Steady-state increase in respiratory rate following a step increase/decrease in exercise intensity during CLT	1/min
Oxygen cost of work during constant load (VO_2_/P)	Oxygen uptake versus work rate during passive and active constant load phases	mL/min/W

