### Outcome measures

All primary and secondary outcome measurements will be carried out at baseline (t0), after each 4-week intervention period (t1, t2, t3, *etcetera*), and before clinical discharge. At baseline, descriptive variables for each subject include age, sex, area and type of infarct, side of stroke, time since stroke onset, body height and body mass.

A summary of the primary and secondary outcome measures can be found in Table 1. The primary outcome will be aerobic capacity, the accepted criterion for exercise capacity [24]. We will estimate standardised cardiopulmonary performance parameters based on international guidelines [25]. Secondary outcome measures will focus on physical performance, stroke impact, and feasibility. We will evaluate the work rate tracking error during FC-RATE by calculating the root mean square error (RMSE) between actual work rate and target work rate values. Gait speed will be assessed using the 10 Meter Walk Test (10MWT) [26,27]. Walking endurance will be measured using the 6 Minute Walk Test (6MWT), the distance that an individual is able to walk in 6 minutes on a hard, flat surface [28,29]. To assess basic standing function in non-ambulatory subjects, we will employ a standardised standing test on a force plate. The subject will be requested to: (1) stand in bipedal stance, (2) shift his/her body weight from the right to the left leg alternately, and (3) shift his/her body weight in a defined rhythm from the right to the left leg alternately. The test-retest reliability of centre of pressure measures in bipedal tasks has been shown previously [30]. We will use the Stroke Impact Scale (SIS) to assess recovery and quality-of-life after stroke [31].

**Table 1 T1:** Overview of primary and secondary outcomes

**Variable**	**Details**	**Unit**

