### Instrumentation

We will use the Lokomat driven-gait orthosis system (Hocoma AG, Volketswil, Switzerland) integrated with a treadmill (h/p/cosmos sports & medical GmbH, Traunstein, Germany) and a motor-driven body weight support system with real time feedback control for precise body weight unloading (Lokolift, Hocoma AG) to apply RATE. A human-in-the-loop feedback system will control each subject’s active work rate by projecting his mechanical work rate onto a screen at the front of the treadmill together with a target mechanical work rate. Figure 2 illustrates the FC-RATE approach. The subject will be instructed to vary the forces applied on the exoskeleton by volitional muscle activity and to keep the actual work rate as close as possible to the target. This procedure will be used to assess the primary outcome measures (aerobic capacity), and to guide each subject’s individual target work rate during FC-RATE in the experimental group.

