### Intervention

Both groups will receive regular RATE sessions (3/week, 30min/session) during their inpatient rehabilitation period (typically, 4 to 12 weeks). Training intensity will be recorded by continuous heart rate monitoring and evaluating rate of perceived exertion (RPE) on the 6 to 20 scale [38]. The experimental group will receive progressive cardiovascular exercise using FC-RATE. Training will start at 40% of peak work rate (based on initial IET results) for the first session. Intensity will then be adjusted by increasing the target work rate in 5% steps for subsequent sessions based on heart rate and RPE outcomes (target heart rate: 40 to 70% of heart rate reserve, target RPE: 11 to 14). The control group will receive conventional RATE, where therapists will focus on gait quality only. To confirm or refute low cardiovascular training intensity in the control group (target heart rate: ≤30% of heart rate reserve, target RPE: ≤7), therapists will monitor heart rate and RPE during all training sessions. All subjects will receive individually tailored conventional therapy including physiotherapy (4 to 5 sessions/week, 30 to 60min/session), occupational therapy (2 to 3 sessions/week, 30 to 60min/session), and individual speech and language therapy.

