### Data management and analysis

Data will be recorded on standardised forms and concealed between examiners and therapists. All data recorded continuously during testing will be saved automatically by the software module and will only be accessible by an independent software specialist. Data set examples will be checked for errors randomly or at any time a serious adverse event occurs. Raw breath-by-breath data will be processed using a zero phase shift moving average filter over 15 breaths [39]. Peak cardiopulmonary response variables will be calculated by analysing the final 30 s during incremental exercise, whereby criteria for maximal aerobic capacity will be (1) plateau in oxygen uptake, (2) respiratory exchange ratio (RER) ≥1.15, and (3) peak heart rate within 10 beats per minute of the age-predicted heart rate maximum (adjusted for subjects on β-blocker medications) [24]. Further peak performance variables will be defined as the maximal values at the termination time of the IET. The gas exchange threshold (GET) will be estimated using the v-slope method and standard gas exchange criteria [40]. Step response kinetics will be calculated using a non-linear least-squares algorithm to fit the data as described in the following mono-exponential equation: VO_2(t)_=VO_2_(b)+ΔVO_2_(1-e^-(t-Td)/τ^), t > 0, with VO_2_(b) = oxygen uptake at baseline, ΔVO_2_ = step increase in oxygen uptake, Td = time delay of 20 s corresponding to the cardiodynamic phase of the response, and τ = time constant [34]. Steady-state will be defined as the mean value of the final 120 s during constant load phases. All analyses will be performed using MATLAB (Version R2010a, MathWorks, Natick MA, USA) and MetaSoft (Version 3.9.6 SR1, Cortex Biophysik GmbH, Leipzig, Germany).

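### Peak work rate, a listed primary outcome, is a maximum with no stated averaging window, so it depends on tracking skill, which only the experimental arm trains

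*Protocol article*

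**What the plan says.** Table 1 defines Ppeak, under the primary outcomes, as "Maximal work rate during IET". Peak oxygen uptake in the same block is "Peak oxygen uptake in the last 30 s during IET", and peak ventilation and respiratory rate use the same window. (Peak heart rate is also a plain maximum, but it is not a signal the subject steers.)

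The Data management and analysis section makes a similar split. For one group of variables, "Peak cardiopulmonary response variables will be calculated by analysing the final 30 s during incremental exercise". For the rest, "Further peak performance variables will be defined as the maximal values at the termination time of the IET". The only smoothing described is for gas exchange: "Raw breath-by-breath data will be processed using a zero phase shift moving average filter over 15 breaths". None is described for work rate.

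The Instrumentation section says that the subject varies the force on the exoskeleton while watching a screen, "to keep the actual work rate as close as possible to the target". This procedure serves both the primary outcome tests and training in the experimental arm. The Outcome measures section makes tracking error a secondary outcome, obtained by "calculating the root mean square error (RMSE) between actual work rate and target work rate values". Under Intervention, controls receive conventional robotics-assisted treadmill exercise directed at gait quality only. The same section uses Ppeak for dosing: "Training will start at 40% of peak work rate (based on initial IET results) for the first session".

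**The concern.** On a motor-braked ergometer the device largely sets work rate. Here the subject produces it stride by stride, and the protocol expects it to deviate from target. The maximum of a fluctuating signal lies above the level that can be held, and the gap widens with the fluctuation. Two subjects with equal sustainable work rate but different steadiness would get different Ppeak values.

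Randomisation balances steadiness at baseline but not afterwards. One arm practises the tracking task three times a week, typically for 4 to 12 weeks, and the other does not. A post-intervention difference in Ppeak can then mix work capacity with tracking skill. The same figure sets the first training target.

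**Working it through.** The article gives no value for Ppeak, its SD, the tracking error or the work-rate sampling, so there is no stated figure to reproduce. What follows is a simulation under assumptions.

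**Taken from the article**
- The ramp reaches maximal voluntary contraction during walking in about 10 minutes.
- The test stops, among other criteria, after 60 s below target.

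**Assumed**
- True capacity is 50 W, and the target rises to 60 W in 10 minutes (60 W / 600 s = 0.1 W/s).
- There is one value per second with no filter.
- Work rate = min(target, capacity) + tracking error. The error is first-order autoregressive, with SD 5 to 20% of 50 W.

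**Step 1. Size of the inflation.** Mean results over correlations 0 to 0.8, true value 50 W:

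| Definition | Range (W) | Against 50 W |
|---|---|---|
| Whole-test maximum | 55.6 to 78.4 | +11% to +57% |
| Highest 30 s mean | 50.6 to 58.6 | +1% to +17% |
| Last 30 s mean | 47.2 to 50.0 | -6% to 0% |

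For example, 55.6/50 = 1.11 and 78.4/50 = 1.57. At correlation 0.5 the maximum is 56.1, 63.0, 70.0 and 77.8 W for SDs of 5, 10, 15 and 20%. At correlation 0.9 the maximum is 52.2 to 68.9 W (+4% to +38%), and the last 30 s mean falls to 42.3 to 47.4 W, so it too has limits when errors are slow.

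**Step 2. If training steadies the signal.** Correlation 0.5, tracking SD falling from 15% to 10% of 50 W:

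| True change | Change in maximum | Change in last 30 s mean |
|---|---|---|
| +5 W | 68.2 - 70.1 = -1.9 W | 54.8 - 49.4 = +5.4 W |
| +10 W | 73.0 - 70.1 = +2.9 W | 59.7 - 49.4 = +10.3 W |

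If the SD stays at 15%, a true +10 W reads as 80.5 - 70.1 = +10.4 W in the maximum. Unchanged tracking error largely cancels in change scores.

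**Step 3. If poor tracking means undershoot.** With capacity 50 W and SD 5%, a steady shortfall of 2.5 W triggers the 60 s stop sooner. The maximum is 51.7 W, against 56.2 W without the shortfall. Better tracking would then raise Ppeak by 4.5 W with no gain in capacity. The last 30 s mean moves almost as much (46.0 against 50.0 W), so averaging does not cure this.

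**Step 4. The two definitions.** Table 1 searches the whole test; the data analysis section refers to the termination time. In a similar simulation with the stop rule (capacity 1.0, correlation 0.5 to 0.8), the average is 1.10 to 1.55 for the whole-test maximum, 1.07 to 1.30 for the maximum within the final 30 s, and 0.95 to 1.00 for the single value at termination. The reading chosen changes the bias materially.

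**The case against.** The strongest objection is that the article does not say Ppeak is one raw sample. The Figure 2 legend distinguishes raw, total and net mechanical work rate, so some processing chain exists, and a condensed article may leave filtering to the full protocol. In a separate simple ramp model without the stop rule (correlation 0.5), averaging over about 12 s before taking the maximum cuts an inflation of +6 to +37% to about -1 to +9%. This stands as a limit on size. It does not remove the point, because the article does state windows and a filter for gas exchange and fixes a maximum for work rate.

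Second, the data analysis section's wording is narrower than Table 1's and, read as the last value, carries no upward bias. That also stands. It shows that the two definitions differ and that one must be chosen.

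Third, a reader might infer that better tracking after training will cancel real gains in the experimental arm. The documents do not support this. The masking in Step 2 rests on an assumed fall in tracking SD, and Step 3 reverses the direction.

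Fourth, Ppeak is one of 16 variables listed as primary in a pilot trial, and sessions after the first are adjusted by heart rate and perceived exertion. This limits the consequence, but the variable remains a declared primary outcome.

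**Conclusion.** The point holds as a weakness in how a primary outcome is defined. As written, Ppeak is a maximum without a window, taken from a signal that the subject tracks, and only one arm trains the tracking. It therefore depends on tracking skill as well as capacity, and the group comparison can be biased. The upward inflation of an unaveraged maximum is general. Its illustrative size, +11% to +57%, rests on an assumed unsmoothed tracking SD of 5 to 20% of capacity and correlation 0 to 0.8, and would be smaller with filtering. Neither the sign nor the size of the between-group bias can be determined from the article. The change is worth making, because a better definition is available from data already collected.

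**What to change.** In Table 1, define Ppeak as the mean net work rate over a fixed 30 s window of the active phase of the incremental test, preferably the final 30 s already used for peak oxygen uptake. State any filter applied to work rate, and give the same rule in the Data management and analysis section. A highest rolling 30 s mean is a weaker choice: it does not match the window for peak oxygen uptake and keeps some of the upward bias (Step 1). Because the starting training load refers to peak work rate, the Intervention section should say which definition it uses; that is for the investigators to reconcile.

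The cost is a line in each section and a change to the processing code, with no new measurement, since testing data are saved continuously. The reported value will be slightly below an instantaneous peak: if a test stops while work rate is still rising at the assumed 0.1 W/s, a 30 s mean lies 0.1 × 15 = 1.5 W below the end point, or 3% of 50 W. Averaging also leaves any effect of undershoot through the 60 s rule, so Ppeak is best read alongside the tracking error already recorded.

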**Secondary outcomes**		
RMS deviation of work rate RMSE_P_	Work rate tracking error during feedback-controlled robotics-assisted treadmill exercise	W
Gait speed	10 Meter Walk Test (10MWT)	m/s
Walking endurance	6 Minute Walk Test (6MWT)	m
Standing function	Standardised protocol to assess standing using a force plate	%, mm
Quality-of-life	Stroke Impact Scale (SIS)	Score
Feasibility	Criteria for success	4 scale rating

CLT, Constant load testing; IET, incremental exercise testing; RMSE, root mean square error.

The feasibility of the study protocol will be based on defined criteria for success such as compliance, attrition, safety, and successful data processing. We define feasibility to be affirmed with compliance to the study protocol of ≥90%, an attrition rate of ≤10%, clinical safety of 100%, and effective data processing of 100%. The overall feasibility of the study will be rated using the following outcomes: (i) protocol deemed feasible (when all criteria for success can be achieved), (ii) protocol deemed feasible with minor modifications (≥75% of the criteria for success can be achieved), (iii) protocol deemed feasible with major modifications (≥50% of the criteria for success can be achieved), and (iv) protocol deemed not feasible (none of the criteria for success can be achieved) [32].

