### Sample size and power calculation

The required sample size has been calculated based on pooled estimation of standardised effect sizes obtained from a previous meta-analysis on cardiovascular exercise early after stroke [18]. Power analysis was done using G*Power Software (Version 3.1, University of Dusseldorf, Germany). *A priori* analysis indicated that a sample of at least 14 subjects would provide a statistical power of 80%, that is, an 80% (β = 0.2) chance to detect a 20% (α = 0.05) difference between groups. To allow for dropouts, a total of 20 subjects will be recruited.

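### The four-level feasibility rating has no level for a trial that meets one of its four criteria, and "not feasible" applies only if every criterion fails

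*Protocol article*

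**What the plan says.** The rule is in the protocol article, Methods/Design, Outcome measures, in the paragraph below Table 1. Feasibility is to rest on "defined criteria for success such as compliance, attrition, safety, and successful data processing". The next sentence gives each a threshold: "compliance to the study protocol of ≥90%, an attrition rate of ≤10%, clinical safety of 100%, and effective data processing of 100" per cent.

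Four overall ratings follow:

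- Rating (i), the best, needs every criterion to be met.
- Rating (ii) is worded "protocol deemed feasible with minor modifications (≥75% of the criteria for success can be achieved".
- Rating (iii), which calls for major changes, needs at least half of them.
- Rating (iv), the worst, is worded "protocol deemed not feasible (none of the criteria for success can be achieved".

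No criterion is given more weight than another in ratings (ii) to (iv). Table 1 lists feasibility among the secondary outcomes, as a rating with four levels. The end of the Background names the evaluation of feasibility as the second of three aims.

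**The concern.** A graded decision rule should return one level for every result that can occur. This one steps down through all, 75% and 50%, and then jumps to none. Anything above zero and below one half falls between the last two levels.

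The gap lies at the unfavourable end, where a rule fixed in advance is most useful. A study that fails three of four criteria is neither feasible with major modifications nor not feasible. Whoever reports it must pick a label with the results in hand. The Randomisation, allocation concealment, and blinding section says that the project leader will analyse the data, so the choice would probably fall to someone close to the study.

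A lesser matter is that the criteria count equally. The Safety arrangements section acknowledges a risk of recurrent cerebral or cardiac events and says that attachment to the exoskeleton complicates emergency procedures. Yet the rating treats a missed safety criterion like a missed data-processing criterion.

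**Working it through.** The plan states no numerical result for this rule, so there is no figure to reproduce. The check is to apply the rule to every possible result.

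**Inputs (Outcome measures, below Table 1).** Four criteria, each met or not met. The ratings are read from the top down, so a result takes the highest level it satisfies.

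**Step 1: patterns.** Four yes/no criteria give 2^4 = 16 patterns. The number with exactly k criteria met is C(4, k).

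| Criteria met | Share | Patterns | Rating as written |
|---|---|---|---|
| 4 | 100% | 1 | (i) |
| 3 | 75% | 4 | (ii) |
| 2 | 50% | 6 | (iii) |
| 1 | 25% | 4 | none applies |
| 0 | 0% | 1 | (iv) |

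The sum is 1 + 4 + 6 + 4 + 1 = 16. One of the five possible scores, covering 4 of the 16 patterns, has no rating. Rating (iv) covers a single pattern.

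**Step 2: can the gap be reached?** Two of the criteria require 100%. Taking that to mean no failure at all, one safety failure and one data set that cannot be processed miss both. The attrition limit with 20 recruited is 0.10 × 20 = 2 losses; three losses are 3/20 = 15% and miss it. If compliance is met, these few events give 1 of 4 and no verdict. The documents give no probability for each criterion, so the pattern counts describe the rule and are not chances of occurrence.

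**Step 3: does it depend on there being exactly four criteria?** The list is introduced with words that could leave it open, although thresholds are set for these four only. With five criteria, 1/5 = 20% and 2/5 = 40% would be unrated. With six, 1/6 = 17% and 2/6 = 33% would be. The gap remains.

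**Step 4: patterns that fail safety.** Fix safety as not met and let the other three vary: 2^3 = 8 patterns.

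| Other criteria met | Total met | Patterns | Rating as written |
|---|---|---|---|
| 3 | 3 of 4 | 1 | (ii) |
| 2 | 2 of 4 | 3 | (iii) |
| 1 | 1 of 4 | 3 | none applies |
| 0 | 0 of 4 | 1 | (iv) |

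Only one of the eight, with safety as the sole failure, reaches the minor-modifications rating.

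**Step 5: the rule after the change.** With (iv) defined as fewer than 50% met, it covers 4 + 1 = 5 patterns, and 1 + 4 + 6 + 5 = 16 are rated. If rating (ii) is also closed when safety is not met, the safety-only failure moves to (iii): 1 + 3 + 7 + 5 = 16, again complete.

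**The case against.** The strongest reply is about consequence. The rating is a descriptive secondary outcome in a pilot of 20 subjects. It affects neither the primary outcome nor any error rate. A protocol that meets one of four criteria lies below the major-modifications level, and few readers would call it feasible. The Conclusion also ties further trials to reasonable feasibility together with potential for efficacy, and does not refer to the four-level rating. All of this stands and limits the severity. It does not supply the missing level. The scale carries a citation, which cannot be consulted here, but the wording that the trial would apply is the article's own.

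On safety, the reply is that equal weighting is a design choice that no other section contradicts, and that rating (i) already requires 100% safety. Both points are right. A reader might infer that any safety failure is passed off as needing minor modifications. The text does not support that: it happens only when safety is the sole failure. Nor does subject protection depend on the rating, because the test termination criteria and the safety arrangements operate separately.

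A reader might also infer that the attrition limit in "an attrition rate of ≤10%, clinical safety of 100%, and effective data processing of 100" per cent contradicts the sample size section, where at least 14 subjects are needed and "To allow for dropouts, a total of 20 subjects will be recruited". Keeping 14 of 20 tolerates a loss of 6/20 = 30%, three times the 10% limit, and a 10% loss would need only 14/0.90 = 15.6, so 16 recruits. But the section states no expected dropout rate. The 30% is a back-calculated maximum and not a forecast. How much loss the analysis can survive and how little loss counts as success are different questions, and the two figures can differ. The chance of losing at most 2 of 20 is 0.035 if true loss is 30%, 0.21 at 20% and 0.68 at 10%. The low figure rests on a loss rate that the protocol never predicts, so no conflict is shown.

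**Conclusion.** The gap is certain on the text. One of four criteria met has no rating, 4 of 16 patterns are undefined, and the negative rating requires failure on every criterion. The result assumes only that each criterion is judged met or not met and that the levels are read from the top down. It does not depend on the list being limited to four.

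The safety weighting is an optional improvement and not an error. It matters where safety alone fails, a pattern that is now rated (ii).

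Severity is minor to moderate: the rule serves a stated aim and can return no verdict, but it is secondary, belongs to a pilot, and is easily repaired.

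**What to change.** **Main change.** Redefine rating (iv) as fewer than 50% of the criteria for success achieved. Every pattern then has a rating. The cost is one phrase and no new data. The consequence is that a result of 1 of 4 is reported as not feasible, where at present it has no label.

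**Optional change.** Add a sentence that rating (ii) is not available when the safety criterion is not met. A safety-only failure would then be reported at level (iii). The downside is that a favourable rating becomes slightly harder to reach. This is a rule for reporting the study verdict and changes nothing in how subjects are managed.

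Both changes should be made before the feasibility results are known. This point calls for no change to the attrition limit or to the recruitment target.
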